### Randomization and blinding

Participants included in the study will have to sign the participation agreement without having a priori knowledge about their group assignment. Study researchers will also be blind to the group to which the assessed participants will belong. Once the online informed consent has been signed, an independent researcher will perform a “blocked randomization”, guaranteeing that the same number of participants are allocated to each condition (ICBT or WL). This allocation will be performed following a random number sequence generated by the Epidat 4.1 program.

### Sample size

The sample size for the trial was calculated following the method described by Campbell, Julious, and Altman [37], and Freiman, Chalmers, Smith, and Kuebler [38]. G*Power 3 software [39] was used to facilitate power analysis.

Because there is no published research on the effectiveness of ICBT for the treatment of AjD, the sample size was calculated taking into account outcomes found in trials that used the BAI and BDI-II as measures of clinical change after an ICBT intervention in patients with clinical depression or anxiety disorder [40–42]. After reviewing the literature and adopting a more conservative approach, an effect size of .70 was assumed in the present study. Considering a significance level of 5% and a power of 80%, 26 participants in each group would be enough to detect the assumed difference. However, because the literature reveals dropout rates from ICBTs of around 30% [43], a sample of 68 participants will be recruited (34 per group).

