### Data analyses

The statistical package IBM SPSS Statistics version 22.0 for Windows will be used for data analyses. Baseline differences between groups will be explored for continuous and categorical measures using both t-tests and chi-square tests. Repeated-measures ANOVAs will be used to assess within-group changes over time in primary and secondary outcome measures. Effect sizes will be estimated using Cohen’s d. Linear regression models will be used to study the effect of different variables (e.g., gender, age, and treatment expectations) on adherence and response to the intervention. Any participants who do not complete the post-intervention assessment will be considered drop-outs. On the other hand, the number of times each patient uses the program will be used as the measure of adherence.

Before analyzing the data, a review of state-of-the-art analytic methodology for RCT will be carried out in order to ensure the use of the most suitable statistical analyses. Finally, following SPIRIT and CONSORT guideline recommendations, both intention-to-treat and per-protocol analyses will be reported [34, 36].

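### The 26 per group fits the stated inputs only as a one-sided figure, and the 30% dropout allowance was multiplied instead of divided: 68 participants give about 66% two-sided power, not 80%

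*Protocol article*

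**What the plan says.** The Sample size section of the protocol article gives all the inputs in one paragraph. On the effect: "an effect size of .70 was assumed in the present study". On the requirement: "Considering a significance level of 5% and a power of 80%, 26 participants in each group would be enough to detect the assumed difference". It then cites dropout from internet-delivered CBT of around 30% and concludes that "a sample of 68 participants will be recruited (34 per group").

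Two other places bear on the reading. Randomization and blinding sets equal allocation, "guaranteeing that the same number of participants are allocated to each condition (ICBT or WL"). Data analyses defines loss for the whole trial: "Any participants who do not complete the post-intervention assessment will be considered drop-outs". A drop-out in this sense therefore has no post-intervention BDI-II or BAI.

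The article does not state a one-sided test or a directional hypothesis. The sample size paragraph gives no baseline-outcome correlation, covariate adjustment or gain from repeated measurement.

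**The concern.** A 5% significance level with no qualifier is normally read as two-sided. On that reading, 26 per group looks too small for a standardised difference of 0.70 at 80% power. Separately, going from 26 to 34 per group for 30% dropout looks like multiplication by 1.3, which does not leave 26 people after a 30% loss.

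Both errors push the same way, and the 80% is the figure readers will use to interpret the trial. If the true two-sided power is near 66%, the trial would miss an effect of 0.70 about one time in three, while the protocol implies one in five. A null result would then be read as stronger evidence against the programme than it is.

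**Working it through.** **Inputs (Sample size, unless noted).** Effect size d = 0.70; significance level 0.05, sidedness not stated; power 0.80; 26 per group; dropout 0.30; recruited 34 per group, 68 in total; allocation 1:1 (Randomization and blinding).

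**Step 1: reproduce the 26.** For two independent groups, the normal approximation is n per group = 2(z₁₋α* + z₀.₈₀)²/d², where α* is 0.05 one-sided or 0.025 two-sided.

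- One-sided: 2 × (1.645 + 0.842)²/0.49 = 25.2, so 26. The noncentral t calculation gives 25.94, so 26. This matches exactly.
- Two-sided: 2 × (1.960 + 0.842)²/0.49 = 32.0, which rounds up to 33. The noncentral t calculation gives 33.02, so 34. This does not match.

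**Step 2: power at the relevant sizes.** Noncentral t with noncentrality d√(n/2) and 2n − 2 degrees of freedom:

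| n per group | Two-sided 5% | One-sided 5% |
|---|---|---|
| 24 | 66.1% | 77.2% |
| 26 | 69.7% | 80.1% |
| 33 | 79.97% | 87.9% |
| 34 | 81.2% | 88.7% |

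Before any dropout, 26 per group falls about 10 points short of 80% on a two-sided test.

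**Step 3: the dropout allowance.**

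- Route that gives the plan's figure: 26 × 1.30 = 33.8, so 34.
- Route that keeps 26 assessed: 26/(1 − 0.30) = 37.1, so 38 per group (76 in total).
- What 34 leaves: 34 × 0.70 = 23.8, about 24 per group, which is fewer than 26.

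This step does not depend on sidedness or on the choice of test.

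**Step 4: the two together.** With 24 per group assessed, power at d = 0.70 is 66.1% two-sided and 77.2% one-sided. Using 23.8 instead of 24 gives 65.7% two-sided. The effect detectable with 80% two-sided power at 24 per group is d = 0.83.

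**Step 5: recruitment that would match the stated target.** Two-sided, unadjusted, with 30% loss: 33/0.7 = 47.1 (48) by the normal approximation, or 34/0.7 = 48.6 (49) by the t calculation. That is 96 to 98 in total. If a one-sided 5% test were intended and declared, the total would be 76.

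**The case against.** **The one-sided origin is inferred.** The paragraph names neither the test nor its sidedness. Data analyses mentions repeated-measures ANOVA, and a two-sided between-group test on two measurements with an assumed correlation of 0.5 (f = 0.35) gives 79.96% power at 50 in total and 81.5% at 52, so it also yields 26 per group. ANCOVA with a correlation of about 0.45 yields 26 by the normal approximation. It is therefore not proven how 26 was obtained. However, each of these routes needs a correlation that the article does not give. The repeated-measures version also averages the baseline into the group comparison, and the article ties its ANOVAs to change within groups. The one-sided t-test is the only one of these routes that uses the stated inputs alone. If another was used, the paragraph omits the assumption on which its number rests.

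**The 30% may apply to the intervention arm only.** The cited rate concerns people who start an online programme, and waiting-list participants start only after their second assessment. With 24 against 34, power is 73% two-sided and 83% one-sided. So the shortfall under a one-sided test depends on loss in both arms, and this part of the objection stands. Equal loss is nevertheless the plan's own treatment: it inflates both arms equally and defines drop-outs for any participant. The two-sided shortfall remains either way.

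**The 66% is a completers figure.** The article promises intention-to-treat as well as per-protocol analyses. An intention-to-treat analysis might recover some information, but by how much cannot be judged from what is shown, and the sample size paragraph claims no such gain.

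**Most of the fall comes from sidedness.** This is true: the inflation error alone takes 80% to 77% one-sided. It is still an error whatever the sidedness.

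**Conclusion.** The point holds. From the stated inputs, 26 per group gives 80% power only one-sided, and no one-sided test is declared. The dropout inflation is wrong on any reading, because 34 per group less 30% is below the plan's own 26.

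Under a two-sided 5% unadjusted comparison with 30% lost in each arm, the planned 68 gives about 66% power at d = 0.70. It gives 73% if only the intervention arm loses 30%, and 81% only if nobody is lost. The one-sided explanation of the 26 is an inference from an exact match; the shortfall of 26 for a two-sided t-test is not. Because the stated power is a headline figure and does not follow from its own inputs, it must be corrected.

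**What to change.** Rewrite the Sample size paragraph and keep 68 as the recruitment figure:

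- State that the test is two-sided at 5%, and name the comparison on which the power is based.
- State that 34 per group gives 81% power for d = 0.70 with no attrition, and about 66% with 30% attrition in both arms, where the detectable effect at 80% power is d = 0.83.
- Replace the dropout inflation by n/(1 − 0.30).

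Alternatively, base the power on a baseline-adjusted comparison (ANCOVA) and declare the baseline-to-post correlation as an assumption. With 24 per group and the effect scaled as d/√(1 − r²), two-sided power is 74% at r = 0.4, 78% at r = 0.5 and 84% at r = 0.6. The article supplies no value of r, so the range should be shown, and the adjusted comparison would have to be the analysis actually planned.

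The cost is one corrected paragraph and a less favourable stated power. No extra participants are needed.

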### Ethics

The protocol for this study has been approved by the Ethics Committee of Universitat Jaume I (Castellón, Spain), and the study will be conducted in compliance with the Declaration of Helsinki and good clinical practice. Participation will be completely voluntary. Participants will also be informed that they may leave the study at any time.

The RCT will be carried out in accordance with current EU and Spanish legislation on privacy and data protection. In order to protect the privacy of the participants, all personally identifiable information will be replaced by a randomly assigned username and only made available to the researchers responsible for its supervision. All data from outcome measures and post-module assessments will be stored separately from the personal information and protected according to AES (*Advanced Encryptation Standard*).

### Study groups

#### Adjustment disorders online (TAO)

Adjustment Disorders Online (TAO) is an ICBT based on a manualized protocol for the treatment of AjD, structured in a therapist handbook and a patient handbook. TAO comprises the following therapeutic components: psychoeducation, techniques to manage negative emotions, exposure, problem-solving techniques, mindfulness, acceptance and elaboration of the stressful event, positive psychology strategies, and relapse prevention. It is the optimized version of the original intervention protocol for AjD developed by Botella et al. [31]. More specifically, TAO also includes behavioral activation for mood disturbance, problem-solving techniques to improve the capacity to deal with everyday challenges, and mindfulness to become aware of the thoughts and feelings related to the stressful event instead of trying to escape from them.

The intervention is easily accessible over the internet at https://www.psicologiaytecnologia.com/. In order to provide a more enjoyable experience, the program content is presented through texts, videos, pictures, vignettes, and interactive exercises. Different contents can also be downloaded as PDF files so that users can review them offline.

TAO is organized into seven sequential modules (see Table 1), and it takes about 7 to 10 weeks to complete it. Although users are encouraged to advance one module per week, some modules may require more time. Therefore, the program also emphasizes that everyone should progress at their own pace, dedicating enough time to understand the module contents and carry out the proposed activities.

**Table 1 Tab1:** TAO content

Module	Aims of the module	Contents
0. Welcome module: starting this program.	- Providing information about TAO. - Promoting the adherence to the program. - Enhancing motivation for change.	- Information about the contents of each module. - Recommendations to get the maximum benefit from the program. - Meditation on reasons to change. - Goal setting.
1. Understanding emotional reactions.	- Providing information about AjD and common reactions to stressful events. - Learning of strategies to manage negative emotions.	- Psychoeducation. - Behavior activation. - Slow breathing technique.
2. Learning to deal with negative emotions.	- Facing avoided situations that contribute to the maintenance of the problem. - Improving the ability to deal with everyday challenges.	- Exposure. - Problem solving technique.
3. Accepting problems.	- Becoming aware of the personal experiences related to the stressful event. - Elaborating and processing the stressful event through the acceptance of the problematic situation.	- Mindfulness. - The Book of Life: Acceptance. - Elaboration of a metaphorical meaning for the stressful event.
4. Learning form problems.	- Starting to see problems as opportunities to grow and learn. - Elaborating and processing the stressful event through the confrontation of the problematic situation. - Promoting personal growth.	- Psychoeducation on the positive contribution of problems. - The Book of Life: Confrontation. - Development of personal strengths.
5. Changing the meaning of problems.	- Elaborating and processing the stressful event through the development of a new meaning for the problematic situation. - Developing a new attitude towards problems.	- Elaboration of a new metaphorical meaning for the stressful event. - The Book of Life: Change the meaning. - Letter of projection towards the future. - Choice of a personal life motto.
6. Relapse prevention.	- Assessing achievements accomplished so far. - Reviewing of leaned techniques. - Identifying problematic situations an developing a plan to deal with them.	- Review of the therapeutic achievements. - Action plan to deal with future problems.

All the modules present the same structure: 1) module agenda; 2) therapeutic contents of the module; 3) exercises and activities to put the psychological techniques learned in the module into practice; 4) assessment of the knowledge acquired during the module; 5) tasks to be completed before advancing to the next module; and 6) summary of the module. An effort was made to simplify the language used in TAO to make it easily understood by users, regardless of their socio-demographic features. Regarding the ease of use of TAO, preliminary results obtained in an acceptance and usability study performed with clinical psychologists and patients with AjD showed that the program interface is highly intuitive and user-friendly and does not require any previous training [44].

#### Waiting list control group

Participants on the waiting list group will be assessed before and after a period of 7 weeks. After completing a post-waiting period assessment, they will be offered the TAO program.

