**Methods:**

A two-armed RCT was designed to compare an intervention group to a waiting list control group. Participants from the intervention group will receive TAO, an internet-based program for AjD composed of seven modules. TAO combines CBT and Positive Psychology strategies in order to provide patients with complete support, reducing their clinical symptoms and enhancing their capacity to overcome everyday adversity. Participants will also receive short weekly telephone support. Participants in the control group will be assessed before and after a seven-week waiting period, and then they will be offered the same intervention. Participants will be randomly assigned to one of the 2 groups. Measurements will be taken at five different moments: baseline, post-intervention, and three follow-up periods (3-, 6- and 12-month). BDI-II and BAI will be used as primary outcome measures. Secondary outcomes will be symptoms of AjD, posttraumatic growth, positive and negative affect, and quality of life.

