### Support

Because the literature shows that guided ICBT provides better results than completely unguided interventions [45], all the participants will receive weekly phone support. This support will consist of a short phone call (maximum 10 min) during the intervention stage. The aim of these phone calls will be: 1) to clarify doubts about the use and functioning of TAO; 2) to remind them of the importance of continuing to work on the program contents; and 3) to congratulate them for their effort and achievements. Patients will receive up to 10 telephone calls over a 7–10 week period, and so they will have a maximum of 100 min of therapeutic support. No additional clinical content will be provided during the phone calls.

The support will be provided by experienced psychologists who will have at least a Master’s degree in Clinical Psychology. Before taking part in the trial, they will receive training in order to ensure that everyone provides the same support.

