
Finally, personal growth achieved during the intervention period will also be assessed. According to WHO (1948), health is “A state of complete physical, mental and social well-being, and not merely the absence of disease or infirmity”. Huber et al. [63] also emphasize “the ability to adapt and to self-manage, in the face of social, physical and emotional challenges”. Consequently, the reduction in clinical symptomatology might be insufficient to achieve an optimal state of health. Improvements in coping strategies, however, might increase the ability to successfully overcome future challenges, without developing a sense of helplessness and/or AjD. Therefore, the main goal of TAO is to provide strategies to deal with current and future difficult situations, whether or not they can be resolved.

However, the study has limitations. The main limitation is the lack of an active treatment control group for comparison. However, because AjD is considered a transient condition [3], it is useful to explore whether brief interventions like TAO can prevent the chronification of this disorder and the development of more severe symptomatology. Moreover, given the lack of EBI for AjD, the comparison with a waiting list control group could be the first step in the validation of psychological treatments for this condition. Another limitation is that the decision about whether to include participants or not is based on the AjD diagnosis made using the *Diagnostic Interview for Adjustment Disorders*, which is not a validated instrument. The use of other diagnostic tools, such as the Adjustment disorder new model questionnaire (ADNM-20) [64], would have helped to corroborate the diagnosis. Unfortunately, there are no diagnostic instruments for AjD adapted and validated in Spanish for the beginning of RCT.

On the other hand, one potential difficulty in implementing the study might be the dropout rates. According to the literature, around 30% of those who start an ICBT do not complete the program. Preliminary results on the engagement in the BADI modular intervention for AjD showed a dropout rate of more than 80% in the intervention condition [29]. However, the inclusion of telephone support in the present study and the linear format of the TAO might improve the engagement of the patients who use it.

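### The waiting list is re-assessed at a fixed 7 weeks, but the TAO arm's outcome is tied to the end of a self-paced programme of about 7 to 10 weeks, so any natural improvement in the gap would favour TAO

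*Protocol article*

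**What the plan says.** **Control arm.** The section Waiting list control group states: "Participants on the waiting list group will be assessed before and after a period of 7 weeks". The Methods paragraph of the Abstract agrees: "Participants in the control group will be assessed before and after a seven-week waiting period". After that assessment, controls are offered TAO.

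**TAO arm.** The section Adjustment disorders online (TAO) states: "TAO is organized into seven sequential modules (see Table 1), and it takes about 7 to 10 weeks to complete it". Users are encouraged to do one module a week, but "the program also emphasizes that everyone should progress at their own pace". The Support section uses the same range: "Patients will receive up to 10 telephone calls over a 7–10 week period".

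**Time of the TAO outcome.** The Assessment section lists baseline, post-intervention and three follow-ups. Table 2 labels the second occasion Post-T (post-treatment). It comprises the online questionnaires, an opinion-of-treatment scale and a telephone diagnostic interview. No calendar week is given for it in the TAO arm.

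**Course of the disorder.** The Discussion calls adjustment disorder transient. The Background says that symptoms resolve within 6 months once the stressor or its consequences have ended.

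**Analysis.** Data analyses names repeated-measures ANOVAs for change over time, promises intention-to-treat and per-protocol analyses, and defines a drop-out as someone without a post-intervention assessment. It mentions no term for elapsed time.

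**The concern.** A comparison with a waiting list isolates the treatment effect only if both arms have had the same time to improve without treatment. Here one arm has a fixed date and the other a date that appears to follow the participant's own pace. Any difference in elapsed time goes one way: TAO participants are measured at the same time as controls or later.

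The post assessment carries the whole controlled comparison. Controls are offered TAO afterwards, so the 3-, 6- and 12-month follow-ups cannot replace it. There is also no untreated observation after week 7. A model with elapsed time would have to extrapolate the control course beyond its data, and completion time is itself determined after randomisation. Adjustment for baseline does not address this.

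There is a second, smaller consequence. If the assessment waits for programme completion, the text gives no date for participants who slow down or stop. The protocol expects about 30% drop-out and promises an intention-to-treat analysis, so that group matters.

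**Working it through.** The protocol gives no figure for this bias to reproduce. The check sets the times side by side and then attaches a size under stated assumptions.

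**Step 1: elapsed time by arm.**

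| Arm | Time of outcome | Source |
|---|---|---|
| Waiting list | 7 weeks, fixed | Abstract (Methods); Waiting list control group |
| TAO | post-intervention; programme about 7 to 10 weeks | Assessment and Table 2; TAO section; Support |

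Extra time in the TAO arm: 7 − 7 = 0 weeks up to 10 − 7 = 3 weeks. The maximum is 3/7 = 43% more elapsed time. Seven modules at the encouraged one a week take 7 weeks, so those who keep that pace have no gap.

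**Step 2: inputs for the size.**
- Planned effect 0.70 and 34 per group (Sample size). They serve only as a yardstick.
- Untreated improvement g over 7 weeks: *assumed*, 0.2 to 0.5 SD, at a constant rate. The documents give no rate.
- Mean delay w in the TAO arm: 3 weeks is the upper bound (everyone assessed at week 10). A mean of 1.5 weeks is an illustration, the middle of the 0 to 3 range.

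**Step 3: bias.** Bias = g × w / 7; share of planned effect = bias / 0.70.

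| g (SD over 7 weeks) | w = 1.5: bias (share) | w = 3: bias (share) |
|---|---|---|
| 0.2 | 0.043 (6%) | 0.086 (12%) |
| 0.3 | 0.064 (9%) | 0.129 (18%) |
| 0.4 | 0.086 (12%) | 0.171 (24%) |
| 0.5 | 0.107 (15%) | 0.214 (31%) |

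Example: 0.5 × 3 / 7 = 0.214, and 0.214 / 0.70 = 31%.

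**Step 4: effect on the error rate.** Suppose that TAO has no true effect and that 34 per group are compared on a scale with SD 1. Then SE = √(2/34) = 0.243. A nominal 5% two-sided test rejects with probability Φ(bias/SE − 1.96) + Φ(−bias/SE − 1.96). This is 5.4% to 7.3% at a mean delay of 1.5 weeks and 6.4% to 14.3% at 3 weeks. With a common assessment time the bias is zero and the rate stays at 5%.

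**Step 5: a wider range.** At 0.02 to 0.10 SD per week and 1.5 to 3 extra weeks, the bias runs from 0.02 × 1.5 = 0.03 SD to 0.10 × 3 = 0.30 SD, or 4% to 43% of 0.70. The size therefore depends heavily on figures that the documents do not contain.

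**The case against.** The case on the other side has real weight.

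- **The trigger is inferred.** No section says that the BDI-II and BAI are released when the last module is finished. The reading rests on the labels post-intervention and Post-T and on the programme's duration. Fig. 1 is not shown, and an article may leave assessment windows to the full protocol. This stands as a limit on certainty. It does not remove the mismatch: the article commits to 7 weeks in one arm and to an event after a 7-to-10-week programme in the other.
- **Confounding is partial.** Anyone who finishes in 7 weeks is assessed when controls are. A reader might infer that elapsed time and arm are wholly confounded, or that the TAO arm gains three full weeks. The documents do not support that: three weeks is the end of the stated range, and the mean delay is what biases the comparison.
- **Remission is conditional.** A reader might call the disorder self-remitting. The Background ties resolution to the end of the stressor or its consequences, the diagnostic interview covers current as well as past stressors, and the Discussion also raises the risk of a chronic course. For participants with an ongoing stressor, natural improvement over three weeks may be slight. If recovery slows with time, the constant rate overstates the bias.
- **A common week has a price.** It may measure some users before their last modules, which is a different question from the effect of the completed programme. Post-T also includes a telephone interview, so more than an online setting has to change.

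These points lower the likely size and the severity. They leave the direction of the timing gap unchanged, and they do not provide a way to correct it in analysis.

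**Conclusion.** The concern holds as a timing gap that can only favour TAO if there is natural improvement, in the trial's only controlled BDI-II/BAI comparison. The 7-week and 7-to-10-week statements are in the text. That TAO participants are assessed at programme end is the natural reading, not a stated fact.

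Under the assumed 0.2 to 0.5 SD of untreated improvement over 7 weeks at a constant rate, the bias is at most 0.09 to 0.21 SD (12% to 31% of 0.70), and about 0.04 to 0.11 SD (6% to 15%) at an illustrative mean delay of 1.5 weeks. It could be negligible if most participants finish in 7 weeks or improve little without treatment. The documents therefore do not establish that the result will be materially biased.

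The point should be fixed: it is cheap to settle in advance and cannot be reliably repaired afterwards. It does not by itself invalidate the design.

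**What to change.** Reconcile the Abstract, Waiting list control group, TAO, Support and Assessment sections on one rule for the time of assessment:

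1. Define the primary BDI-II/BAI time point as the same number of weeks from randomisation, with the same window, in both arms. It should apply whatever module has been reached and whether or not the participant has stopped using the programme. The sponsor chooses the week.
2. Schedule the Post-T telephone interview on the same basis.
3. State from which date the 3-, 6- and 12-month follow-ups run.
4. Keep an end-of-programme assessment in the TAO arm as secondary, with the opinion scale there if wanted.

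The length of the programme need not change.

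**Cost.** Protocol wording, the release date of automatic online questionnaires, and the scheduling of one telephone interview. The trade-off lies in the week chosen: an earlier one measures some TAO users before they finish and has some answer twice, while a later one lengthens the wait before controls are offered TAO.
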